### **Plans for addressing missing data**

It is expected that there will be a substantial amount of missing data for BMI, smoking status and alcohol consumption as these variables may not be regularly updated by GP practices. We have considerable expertise within the team in data management of CPRD data and two members (EK and RP) have developed algorithms to impute and model longitudinal trends of BMI, alcohol consumption, and smoking data. We will use logistic regression to ascertain whether other variables (age, gender or comorbidities) predict whether these data are missing. If these variables do not predict the missing data, then we will assume that the data are missing at random. If the data are missing at random, we will impute the missing values using multiple imputation and conduct a sensitivity analysis to investigate the effect of the missing data on the results of the analyses.

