### **Feasibility counts**

Earlier reports on AF prevalence in England estimated that 2.5% of the population have AF for both valvular and non-valvular AF (NVAf), with increasing prevalence in older age-groups. A previous study, that used CPRD GOLD to identify incident cases of NVAf, identified around 91,000 cases from 2001 to 2013. We conducted a simple feasibility count for incident cases of NVAf patients in CPRD GOLD, and we identified at least 120,000 incident cases are expected for the period (2009-2019) with an annual average of around 11,000 new cases. According to a previous study in the UK that estimated the proportion of AF patients at risk for stroke but did not receive either OACs or antiplatelets to be around 12% of total AF cases. Therefore, we expect to identify around 14,000 NVAf patients not treated with OACs across the duration of the study

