**Covariates:**

- Patients' demographic information (age, gender, ethnicity, body mass index (BMI), geographic location (rural vs. urban), smoking status, alcohol consumption, Charlson comorbidity index for the severity of comorbidity (Appendix 4), electronic frailty index (eFI), and the index of multiple deprivation (IMD).
- For the sub-group of patients with NVAf and history of cancer, cancer diagnosis will be assessed at the index date of NVAf diagnosis and classified by cancer type into breast, prostate, colorectal, haematological, lung, and other types, and by cancer metastasis status.
- Drugs that affect either stroke or bleeding, or commonly interact with OACs, such as antihypertensive drugs, statins, antiarrhythmics, antidiabetic drugs, anticonvulsants, non-steroidal

anti-inflammatory drugs, corticosteroids, systemic azoles, HIV protease inhibitors and ciclosporin. (Appendix 2).

- The CHA2DS2-VASc stroke risk score that consists of 9 points, one for each of: congestive heart failure (CHF), hypertension (HTN), age  $\geq 75$  years (x 2 points), diabetes mellitus (DM), prior stroke or transient ischemic attack (TIA) or thromboembolism (x 2 points), vascular disease, age 65 to 74 years, and sex category. Information included in the CHA2DS2-VASc score will be identified using Read codes (Appendix 3 and 4), except for age and sex, to build the score and assess the risk of stroke for all included patients in the cohort. Further categorization of eligibility for OACs will be carried according to individual CHA2DS2-VASc scores; “not eligible for OAC” if CHA2DS2-VASc score = 0 in males, or 1 in females; and “OAC eligible” if CHA2DS2-VASc score  $\geq 1$  in males, or  $\geq 2$  in females.

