## **Data/statistical analysis**

1. Phase 1 - NVAF cohort: Annual and crude incidence rates of NVAF cases will be calculated and expressed as person-time at risk with 95% confidence intervals (95% CI). Incidence rates will be calculated by dividing the number of new diagnosed NVAF cases each year by the total population at risk during the same year. NVAF incidence in each calendar year of the study period (2009-2018) will be stratified by age and further standardized by age and deprivation quantiles. Status of anticoagulation therapy will be classified as either OAC prescribed or OAC not prescribed. OAC prescribed patients are those who received prescriptions for OACs during the study period. Treatment patterns for OAC users will be evaluated for OACs continuation, discontinuation or switched). OACs not prescribed will be defined as no prescription record of an OACs at any time after NVAF diagnosis, this will also include patients prescribed lone antiplatelet therapy. Proportions of patients prescribed antiplatelets will be described for both OACs prescribed and not prescribed patients. Baseline demographic, and clinical characteristics, and status of cancer diagnosis across OACs prescribed and not prescribed groups will be presented as number and percentage, mean $\pm$  (SD), or median (interquartile range), as appropriate. For both groups' eligibility for OACs will be described and categorized based on stroke risk according to CHA2DS2-VASc score. Trends in OACs initiation, switching from antiplatelet only to OACs, and from VKA to NOAC will be explored for each year and further stratified by eligibility for OACs and deprivation quantiles. To identify variables independently associated with OACs prescribing multivariate logistic regression models will be used and fitted with the covariates described in section N. Similarly, in a separate analysis for patients with NVAF and previously diagnosed cancer multivariate logistic regression models will be fitted to explore variables independently associated with OACs prescribing (i.e, cancer types and metastasis status). The level of statistical significance was set at  $P < 0.05$ .

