## Limitations of study design

Data on patient characteristics and other covariates included in this study may not be fully complete in CPRD. One of the foremost limitations of this analysis was that we will not be able to calculate a full HAS-BLED and HEMORR2HAGES scores for each patient, and therefore fully ascertain bleeding risk, (as a high risk of bleeding may have led to an anticoagulant not being prescribed). Imputation methods will be explored and applied to minimize the impact of the missing data. Sensitivity analysis will also be carried to investigate the effect of the missing data on the results of the analysis, these includes alcohol consumption and labile INR for the calculation of HAS-BLED, and genetic factors included in the HEMORR2HAGES score. Due to the retrospective nature of the study, data on adherence to OACs may not be well recorded and difficult to assess. Also, we might not be able to capture the exact timing of reinitiating OACs after MB events, since some patients might resume anticoagulation in hospital settings and such information will not be available through HES APC linkage.

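### The missing-data rule has its criterion reversed: it assumes missing at random, and imputes, when observed variables do not predict missingness, and states no action when they do

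*Protocol*

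**What the plan says.** The section on plans for addressing missing data sets out a chain of four steps.

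- The problem: "It is expected that there will be a substantial amount of missing data for BMI, smoking status and alcohol consumption". No percentage is given.
- The test: "We will use logistic regression to ascertain whether other variables (age, gender or comorbidities) predict whether these data are missing".
- The inference from a null test: "If these variables do not predict the missing data, then we will assume that the data are missing at random".
- The action: "If the data are missing at random, we will impute the missing values using multiple imputation". A sensitivity analysis on the effect of the missing data is part of the same conditional sentence.

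The section does not say what happens if the variables do predict missingness. It gives no cut-off for deciding whether they do.

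The limitations section speaks of imputation with no condition attached: "Imputation methods will be explored and applied to minimize the impact of the missing data". It also promises a sensitivity analysis. It neither repeats nor withdraws the test.

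**The concern.** A test of whether observed variables predict missingness bears on one question: whether the data could be missing completely at random. If nothing observed predicts missingness, the data are compatible with that mechanism, complete cases are already representative, and imputation offers at most some precision. If observed variables do predict missingness, that mechanism is ruled out. Missing at random given those variables then becomes the natural working assumption, and imputation that conditions on them can remove bias. The protocol attaches imputation to the first result and is silent on the second.

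A null result also gives no protection against missingness that depends on the unseen value itself. If heavy drinkers are less likely to have alcohol recorded, and this is unrelated to age, gender and comorbidity, the test passes and the assumption drawn from it is false.

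BMI, smoking and alcohol are listed covariates in Phases 1 and 3. They enter the Phase 1 models of anticoagulant prescribing and the Phase 3 model of resumption after bleeding. Smoking is also an input to the GARFIELD-AF model. If the rule were followed to the letter and the unstated branch defaulted to complete cases, these analyses would lose patients and precision, and descriptive summaries of the three variables could be biased. Regression coefficients could be biased too if missingness also depends on the outcome, for example on whether an anticoagulant was prescribed.

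**Working it through.** The protocol states no figure that depends on this rule, so there is none to reproduce. The check has three parts.

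**1. How sensitive is the test in Phase 1?**

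Inputs: at least 120,000 incident cases (Feasibility counts; a count in CPRD GOLD alone). The 0.05 level is stated for Phase 1 in the statistical analysis section and is assumed here for the missingness test. Missingness of 20% to 30% is assumed, as is a binary predictor that splits the cohort into two groups of 60,000.

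Formula: SE(log OR) ≈ √(2 / (60,000 × p × (1 − p))), with p the proportion missing.

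- p = 0.30: √(2 / 12,600) = 0.0126. Significant at OR = exp(1.96 × 0.0126) = 1.025; 80% power at exp(2.80 × 0.0126) = 1.036.
- p = 0.20: √(2 / 9,600) = 0.0144. Significant at OR = exp(1.96 × 0.0144) = 1.029; 80% power at exp(2.80 × 0.0144) = 1.041.

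The same question as a difference in proportion missing, from a base of 20%, with power = Φ(difference / SE − 1.96):

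| Patients tested | 0.5 point | 1 point | 2 points |
|---|---|---|---|
| 120,000 | 0.58 | 0.99 | about 1.00 |
| 14,000 | 0.11 | 0.31 | 0.83 |

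For 1 point at 120,000: SE = √((0.20 × 0.80 + 0.21 × 0.79) / 60,000) = 0.00233; 0.01 / 0.00233 − 1.96 = 2.33; Φ(2.33) = 0.99. The 14,000 row only illustrates a smaller set; it is the number of untreated patients that the protocol expects.

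**2. How often does the test find a predictor when there is none?**

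The number of comorbidities tested is not stated. For k independent predictors at 0.05, the chance of at least one significant result under missing completely at random is 1 − 0.95^k: 14% for k = 3, 40% for k = 10, 64% for k = 20.

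**3. What does the rule do under each mechanism?**

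Simulation with assumed settings: 20,000 patients, 200 replicates, about 30% missing, 5 imputations, age as the only observed predictor. The target is the mean of a BMI-like variable, with bias in SD units. In the second row the logit of missingness is −1 + age (standardised), and the variable correlates 0.5 with age. In the third row the logit is −1 + the variable itself, which is unrelated to age.

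| True mechanism | Test finds a predictor | Result under the rule | Complete-case bias | Imputation bias |
|---|---|---|---|---|
| Missing completely at random | 6% | usually imputes | 0.000 | 0.000 |
| Missing at random given age | 100% | no action stated | −0.128 | 0.000 |
| Not at random, unrelated to age | 5% | usually imputes | −0.255 | −0.255 |

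In these settings the rule calls for imputation where imputation changes nothing, and does not call for it in the one row where it removes the bias.

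**The case against.** Several points on the other side stand, and they limit how far the finding reaches.

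- A reader might infer that imputation is switched off whenever it is needed. The missing-data section says if, not only if, and does not prescribe complete-case analysis. It mentions team algorithms for imputing these variables, and the limitations section promises imputation without condition. A separate statistical analysis plan, not shown, might settle the unstated branch. But the test has no evident purpose unless imputation depends on it, and the limitations section does not correct the criterion.
- Missing completely at random is a special case of missing at random, so assuming the latter after a null test is not false in itself. The fault lies in using non-prediction as the criterion.
- Complete-case regression stays consistent when missingness depends only on covariates in the model, because the outcome given those covariates is distributed alike in complete and incomplete records. Age, gender and the comorbidity index are Phase 1 and Phase 3 covariates. The simulation above concerns a mean, not a regression coefficient. The loss may then be mainly in precision and in the descriptive tables.
- A reader might infer that all the risk scores are compromised. BMI and smoking are in neither HAS-BLED nor HEMORR2HAGES, whose alcohol items are scored from diagnostic codes. GARFIELD-AF uses smoking and weight, not alcohol.
- A reader might infer that the main Phase 2 comparison fails. Its propensity list names neither BMI nor smoking, and lists alcohol abuse as a condition. The Cox adjusters named for Phases 2 and 3 include none of the three variables. Cross-references to the wider covariate list leave some exposure, but no more than that is shown.

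**Conclusion.** Wrong as written; should be fixed. The criterion for assuming missing at random and for imputing is reversed, the test cannot support the assumption drawn from it, and the missing-data section does not agree with the unconditional statement under limitations.

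In Phase 1, with about 120,000 patients, 20% to 30% missing and a 0.05 cut-off, associations with odds ratios of about 1.03 would count as prediction, so the branch that leads to imputation would rarely be met. The missingness range and the use of 0.05 for this test are assumptions. It would be tempting to say the same of Phase 3, but that cohort contains only anticoagulated patients with a major bleed. Its size is not given, and the test loses sensitivity quickly in smaller sets. The same variable might therefore be imputed in one phase and not in another.

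The clear effect is on the Phase 1 prescribing models, which the protocol describes as hypothesis generating, on the Phase 3 resumption model, and on the smoking input to GARFIELD-AF. Bias in the regression coefficients is possible, not demonstrated: it requires missingness to depend on the outcome as well, which the planned test does not examine.

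**What to change.** Rewrite the paragraph on missing data as follows.

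1. Remove the missingness regression as a precondition for imputation. It may stay as a description and as a guide to which variables belong in the imputation model.
2. State missing at random, given the variables in the imputation model, as a working assumption that the data cannot test.
3. Use multiple imputation for BMI, smoking and alcohol whatever the missingness regression shows. Include predictors of missingness, exposure, outcome and all covariates of the analysis model.
4. Report complete-case analysis as the sensitivity analysis already planned. A delta-shifted, not-at-random imputation is an optional addition.
5. Align the limitations section with this text.

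The cost is about one paragraph of wording. Imputation and a sensitivity analysis are already in the plan, so no new data are needed and little new analysis.

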### **Patient or user group involvement**

The University of Manchester is home to several established PPIE groups working in areas highly relevant to this proposal including e-health research, primary care, and patient safety. With the help of PRIMER (Primary Care Research in Manchester Engagement Resource) group based at the Centre for Primary Care and Health Services Research, we plan to have at least two PPIE partners with NVAF involved in this study throughout, with links to wider patient groups. They will provide feedback on all aspects, focusing on communication of findings and implications

### **Plans for disseminating & communicating**

Results will be disseminated through the publication of academic papers, conference posters or presentations and a PhD thesis.

## Limitations of study design

Data on patient characteristics and other covariates included in this study may not be fully complete in CPRD. One of the foremost limitations of this analysis was that we will not be able to calculate a full HAS-BLED and HEMORR2HAGES scores for each patient, and therefore fully ascertain bleeding risk, (as a high risk of bleeding may have led to an anticoagulant not being prescribed). Imputation methods will be explored and applied to minimize the impact of the missing data. Sensitivity analysis will also be carried to investigate the effect of the missing data on the results of the analysis, these includes alcohol consumption and labile INR for the calculation of HAS-BLED, and genetic factors included in the HEMORR2HAGES score. Due to the retrospective nature of the study, data on adherence to OACs may not be well recorded and difficult to assess. Also, we might not be able to capture the exact timing of reinitiating OACs after MB events, since some patients might resume anticoagulation in hospital settings and such information will not be available through HES APC linkage.

## **Appendices**

## **Grant ID**
